### Assessments

The following variables are documented during the baseline visit: sociodemographic (age, gender, laterality, professional and marital status); medical history (length of illness, duration of current episode; psychiatric and addictive comorbidities; somatic history; treatments prescribed; degree of prior therapeutic resistance according to the Maudsley Staging Model (MSM) [29]; basal personality according to Cloninger’s Temperament and Character Inventory (TCI) [30]).

The following variables are evaluated at the beginning and end of treatment, as shown in Table 1: intensity of the depression according to the MADRS [25]; the Beck Depression Inventory 13 items (BDI 13) [26] and Clinical Global Impression – Severity (CGI-S) [27]; and quality of life with the Short-Form 36 Health Survey (SF-36) [28]. Response will be defined by a 50% reduction of MADRS or BDI score, and remission by a MADRS score of <8 and a BDI score of <10.

Potential explanatory variables to predict treatment response in addition to sociodemographic and anamnestic data are: clinical dimensions according to the Echelle de Ralentissement Dépressif (ERD) (Depression Retardation Scale) [31], the lack of pleasure Snaith-Hamilton Pleasure Scale (SHAPS) [32] and Starkstein’s Apathy Scale (SAS) [33]; cognitive functions according to the Montreal Cognitive Assessment (MoCA) [34], the Verbal Fluency Test [35] [36], the Modified Card Sorting Test (MCST) [37], the digit span, the Wechsler Adult Intelligence Scale (WAIS IV) [38] and the Trail Making Test [39]; psychomotor retardation using specific tests such as the Finger Taping Test (FTT) [40, 41], the prehensile motor strength test [42], a test to measure information processing speed (currently being validated by our team [43]); and neurophysiological measurements of cortical excitability, namely the cortical motor threshold, short intracortical inhibition (SICI) and intracortical facilitation (ICF) expressed as a percentage compared to the base value, and similarly for the cortical silent period (CSP), which is carried out in both hemispheres [44–46]. All these scales are validated scales. Concerning the motor retardation assessment, we recently showed that administering a battery of psychomotor tests during rTMS sessions is feasible, free of adverse effects and well-tolerated by that population [43]. Cortical excitability is used in daily practice for patients with neurodegenerative troubles with an excellent tolerance and feasibility. Those measures are not performed the same day (interval maximum 72 h) to avoid participant overstimulation. An incentive of €80 is planned for cortical excitability ancillatory measures.

The following scales are evaluated on a weekly basis: the MADRS, the BDI and the CGI to investigate the response kinetics and 1 month, 3 months and 6 months after the endpoint as well as quality of life (SF-36). Data collected directly from participants themselves will be the BDI, the SAS, the SHAPS, the TCI and the SF-36. Adherence to study quality standards is carried out by an independent research associate. All significant adverse events will be reported in the e-CRF by the research team.

### Interventions

For the rTMS, an eight-shaped coil (Cool B65) and a Magpro Stimulator X100 (Dantec Company, Copenhagen, Denmark) are used. The resting motor threshold (RMT) is recorded daily by a Natus Keypoint® (Natus, Middleton, WI, USA). This is defined as the intensity required to elicit at least five motor-evoked potentials (MEPs) with a 50-μV peak-to-peak amplitude out of ten consecutive stimulations when the coil is placed over the left primary cortex (site for maximal stimulation of the abductor pollicis brevis muscle). The parameters used for HF-rTMS delivery are: 110% of RMT; 10 Hz; 20 min; 4 s per train; 28 s intertrain interval; 1600 pulses per day (40 trains of 40 pulses each). The iTBS protocol will be: 80% of RMT; 50 Hz; 6 min; 600 pulses a day.

The target is left DLPFC corresponding to the junction between Brodmann areas 9 and 46 according to an individual’s 3D-MRI. During rTMS sessions, participants are instructed to keep their eyes open and to be relaxed. All subjects are evaluated before, once a week during the rTMS course, at the endpoint and then at 1, 3 and 6 months.

### Primary outcome measures

The primary endpoint in our study will be the number of responders per group, defined by a decrease of at least 50% in the initial MADRS score at the end of rTMS sessions.

### Secondary outcome measures

The secondary endpoints will be: therapeutic response rate corresponding to a MADRS score improvement of >50% in each group 1 month after rTMS sessions; number of remissions defined by a MADRS score of <8 at the endpoint and 1 month after; number of therapeutic responses and remissions maintained in the 6 months following rTMS treatment; changes in quality of life; and clinical, motor, neuropsychological and neurophysiological (cortical excitability) therapeutic response markers.

### Statistical analysis

A descriptive analysis of the data collected during each patient evaluation will be carried out up until the final evaluation. Specific time points for analysis are: end of rTMS sessions and, 1, 3 and 6 months after the treatment course. Continuous variables will be described using median and range; and qualitative variables using frequencies and percentages.

The final analysis will be conducted according to the intent-to-treat (ITT) principle. The starting hypothesis is a 25% response rate in the 10-Hz group in accordance with 10-Hz HF-rTMS trials of reference [5] and 60% in the iTBS group based on pilot studies [17]. Assuming a 5% (bilateral) type I error and a power of 80%, a total of 60 subjects is required (calculated using SAS software).

The therapeutic response rates (proportion of responders) in each group will be compared using a chi-squared test (or Fisher’s exact test, if appropriate). Estimates of absolute and relative differences (via the odds ratio or relative risk) in terms of efficacy will be provided with their corresponding 95% confidence intervals. The format of the outcome data used for each participant for analysis will be changes from baseline.

Changes in quantitative variables over time (evaluation of the therapeutic effect of rTMS (iTBS) on variations in the MADRS, BDI and CGI scores) will be analysed using random effect models allowing to take into account the repeated measurements. Time (baseline, after 5, 10, 15, and 20 sessions, +1 month, +3 months and +6 months) and group (iTBS or standard) effects will be estimated and tested as well as an interaction with group. Changes in other quantitative variables over time will be investigated according to the same strategy.

The analysis and comparison between groups of the onset of relapse of depression in the 6 months will be carried out using a logistic regression model and testing factors linked to the therapeutic response (neuropsychological and motor tests, dimensional scales, initial measurements of cortical excitability).

Concerning the risk of missing data, a very low attrition rate is expected, below 5% [47] because of the well-known high tolerance to rTMS and iTBS [48]. In case of withdrawal of consent, patients will not be included in final analysis – they will be replaced.

Missing data will be described in terms of frequencies and percentage for each group. Imbalances will be evaluated by the chi-squared test (or Fisher’s exact test). Comparison of missing data onset during follow-up will be realised with a log-rank test for longitudinal data. Each dropout will be described as follows: arm, exit date, exit reason, characteristics at inclusion and last data collected. In case of missing data, despite every effort to prevent it, a multiple imputation analysis will be performed.

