### Noninclusion criteria

Patients presenting with at least one of the following criteria are not be enrolled in the study: diagnosis of a bipolar disorder; schizophrenia; addiction; neurodegenerative disease; use of benzodiazepines (unless prescribed over 3 months earlier at a stable dosage); use of mood-modifying treatments (thyroid extracts, interferon, corticosteroids); previous failure of ECT therapy; anticonvulsant treatment; contraindication to magnetic resonance imaging (MRI); contraindication to the practice of rTMS: history of convulsions, progressive neurological and neurosurgical disorders; any prosthetic material or foreign body in situ (pacemaker, implantable defibrillator); minors or persons deprived of liberty following a legal or administrative decision or hospitalised without consent, in guardianship; or pregnant women or women of child-bearing age who are not using contraception because of no available data about iTBS and pregnancy (these women could receive, if absolutely necessary, from case to case, conventional rTMS treatment, outside the study). The same applies for subjects unable to guarantee longitudinal follow-up.

In case of a serious adverse event or exacerbated symptoms of depression, blind status will be lifted and patients will receive appropriate care and retained in the follow-up.

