#### Randomisation

During the baseline inclusion visit, the inclusion/exclusion criteria are checked and participants randomised into two groups by a computerised random number generator with a permuted block design (ratio 1:1) without stratification or minimisation. Block size and type of variation (fixed or randomly) are not yet known by the investigators to maintain adequate blinding. Randomisation occurs in a recorded delay of maximum 72 h before first rTMS session.

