#### Follow-up

Investigators will meet participants 1, 3 and 6 months after the last rTMS session.

A patient who fails to respond to therapy (no decrease of over 50% in the MADRS score) despite 4 weeks of treatment will continue longitudinal follow-up in order to avoid selection bias. A telephone call is made in the second, fourth and fifth month outside the follow-up consultations to keep in contact with patients and remind them of the next appointment in order to avoid their being lost to follow-up.

The study will last 33 months in total with 24 months being the enrolment period. Patients are followed up over a period of approximately 34 weeks in total (Table 1).

**Table 1 Tab1:** Flow chart

Clinical trial										
Study period	Pre-enrolment	Inclusion and randomisation	Trial period							
			rTMS treatment					Follow-up phase		
Clinical visits	V1 information	V2 (D − 3)	V3 AD0 Start of rTMS treatment	V4 D7 (±2D) After 5 sessions	V5 D14 (±2D) After 10 sessions	V6 D21 (±2D) After 15 sessions	V7 D28 (±2D) After 20 sessions	V8 M1 (±7D)	V9 M3 (±7D)	V10 M6 (±7D)
Length of time compared to randomisation	−21 to 42 days	0								
Inclusion/exclusion criteria	X	X	X	X	X	X				
Signed Consent Form	X	Verification								
Medical history	X									
MRI	X	Target labelling								
Concomitant treatments	X	X	X	X	X	X	X	X	X	X
Motor threshold titration			X	X	X	X	X			
Routine clinical examination	X	X	X	X	X	X	X	X	X	X
MADRS, CGI, BDI		X		X	X	X	X	X	X	X
SAS, SHAPS, MoCA, ERD, HARD		X					X	X		
MSM, TCI		X								
TMT MCST Verbal fluency		X					X	X		
FTT Prehensile motor strength Reaction times		X					X	X		
SF-36		X					X	X	X	X
Adverse events			X	X	X	X	X	X	X	X
Ancillary cortical excitability study										
Biophysical measurements			X				X			
Signed Consent Form	X	Verification								

*BDI* Beck Depression Inventory, *CGI* Clinical Global Impression, *ERD* Echelle de Ralentissement Dépressif, *FTT* Finger Taping Test, *HARD scale* Humeur, Anxiété, Ralentissement, Danger, *MADRS* Montgomery and Adsberg Rating Scale, *MCST* Modified Card Sorting Test, *MoCA* Montreal Cognitive Assessment, *MRI* magnetic resonance imaging, *MSM* Maudsley Staging Model, *rTMS* repetitive transcranial magnetic stimulation, *SAS* Starkstein’s Apathy Scale, *SF-36* Short-Form 36, *SHAPS* Snaith-Hamilton Pleasure Scale, *TCI* Temperament and Character Inventory, *TMT* Trail Making Test

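### Excluding and replacing patients who withdraw consent, with no limit to withdrawals before randomisation, contradicts the promised intention-to-treat analysis

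*Protocol article*

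**What the plan says.** All references are to the protocol article.

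- **Statistical analysis, analysis principle:** "The final analysis will be conducted according to the intent-to-treat (ITT) principle".
- **Statistical analysis, consent withdrawal:** when consent is withdrawn, "patients will not be included in final analysis", and replacements are to be recruited. The same paragraph expects attrition below 5%.
- **Statistical analysis, missing data:** "In case of missing data, despite every effort to prevent it, a multiple imputation analysis will be performed". Each dropout is also to be described by arm, exit date, reason, baseline characteristics and last data collected.
- **Randomisation:** "Randomisation occurs in a recorded delay of maximum 72 h before first rTMS session". Consent is signed earlier, at the screening visit (Study process and Table 1).
- **Follow-up:** a patient who does not respond after four weeks "will continue longitudinal follow-up in order to avoid selection bias".
- **Noninclusion criteria:** after a serious adverse event or worsening of depression, "blind status will be lifted and patients will receive appropriate care and retained in the follow-up".
- **Primary outcome measures:** the endpoint is the number of responders per group at the end of the sessions, a responder being a patient whose MADRS score has fallen by at least half.

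**The concern.** Intention to treat keeps every randomised patient in the allocated arm. A rule that takes randomised patients out of the analysis set and recruits others in their place defines a different set. The withdrawal sentence has no time limit. Read literally, it reaches a patient who leaves after 15 sessions, and even one who leaves during follow-up after the primary endpoint has been measured.

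Withdrawal of consent during a 20-session course for resistant depression may well be linked to lack of benefit or poor tolerance. If so, those removed are not a random sample of their arm, and a replacement is a new draw from the population, not a stand-in for the patient who left. If the number or reasons differ between arms, the primary comparison loses the protection of randomisation for those patients. The multiple imputation does not repair this, because a patient outside the analysis set is not imputed.

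There is also a practical risk. With two incompatible statements in the plan, someone must later choose between them, possibly knowing which choice favours which result.

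**Working it through.** **1. The plan's own sample size.** Inputs from Statistical analysis: 25% versus 60% response, two-sided alpha 0.05, power 80%, total 60. With pooled variance and no continuity correction, the mean rate is (0.25 + 0.60)/2 = 0.425 and

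n per arm = [1.960·√(2·0.425·0.575) + 0.842·√(0.25·0.75 + 0.60·0.40)]² / 0.35² = 30.1, rounded up to 31 (62 in total).

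The arcsine formula gives 30 per arm (60 in total). At 30 per arm the pooled formula gives 79.9% power, and exact enumeration of the uncorrected chi-squared test gives 80.2%. The stated 60 reproduces, so the fault lies in the analysis set and not in the sample size.

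**2. Which patients each statement covers.**

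| Patient | Treatment in the plan | Consistent with ITT? |
|---|---|---|
| Non-responder at 4 weeks | Stays in follow-up | Yes |
| Serious adverse event or worsening | Unblinded, stays in follow-up | Yes |
| Other missing data | Multiple imputation | Yes |
| Consent withdrawn between screening and randomisation | Excluded, replaced | Yes, never randomised |
| Consent withdrawn after randomisation | Excluded, replaced | No |

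Only the last row conflicts. Since randomisation is at most 72 hours before the first session, any withdrawal during treatment falls in that row.

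**3. Average bias.** Suppose a share d of one arm withdraws, all of them non-responders (assumption), and the other arm has no withdrawals. The analysed response rate in that arm becomes p/(1 − d). I take p = 25% (the plan's control rate) and p = 40% (assumption), with the same true rate p in both arms. Type I error is for the uncorrected chi-squared test with 30 analysed per arm; without withdrawals it is about 4.9%.

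| d (assumed) | p = 25% becomes | p = 40% becomes | Bias, points | Type I error |
|---|---|---|---|---|
| 5% | 26.3% | 42.1% | 1.3 to 2.1 | 5.1–5.2% |
| 10% | 27.8% | 44.4% | 2.8 to 4.4 | 5.6–6.4% |
| 15% | 29.4% | 47.1% | 4.4 to 7.1 | 6.6–8.6% |

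**4. A single borderline result.** Assumed counts: 62 randomised, iTBS 16/32 and 10-Hz 8/30 responders, with two iTBS patients withdrawing as non-responders. Two of 62 is 3.2%, within the expected attrition. The uncorrected statistic is X² = N(ad − bc)²/(product of the four margins).

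- All randomised, withdrawals as non-responders: difference 50.0 − 26.7 = 23.3 points. X² = 62·(16·22 − 16·8)²/(32·30·24·38) = 3.55, p = 0.059. Fisher's exact p = 0.072.
- Two withdrawals excluded, 16/30 versus 8/30: difference 53.3 − 26.7 = 26.7 points before rounding of the rates. X² = 60·(16·22 − 14·8)²/(30·30·24·36) = 4.44, p = 0.035. Fisher's exact p = 0.064.

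Exclusion alone takes the chi-squared result across 0.05. Fisher's test, which the plan allows where appropriate, does not cross.

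**5. Near the planned effect.** 30 × 0.60 = 18 and 30 × 0.25 = 7.5, taken as 8. The comparison 18/30 versus 8/30 gives p = 0.009. Keeping two further iTBS withdrawals as non-responders, 18/32 versus 8/30, gives p = 0.018. The conclusion does not change.

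**The case against.** **Part of the rule is harmless.** Consent comes before randomisation, and the sentence does not say that it concerns randomised patients. Replacing people who leave in that interval breaches nothing. This stands, but the sentence is not confined to that interval and no other section confines it.

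**Withdrawn consent may oblige the sponsor to stop using data.** The article gives no such reason. A request for erasure would justify omitting that patient's data, not a general exclusion with replacement.

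**The exclusions would be visible.** Each dropout is to be described by arm, date and reason, so a reader could redo the analysis with withdrawals as non-responders. True, but the primary result would still come from the reduced set.

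**The effect is small.** Expected attrition is below 5%, and consent withdrawal is only part of attrition. This stands. It limits the likely damage but does not remove the contradiction, and the attrition rate is a forecast.

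Two stronger readings are tempting and are not supported:

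- A reader might infer that the primary analysis becomes one of completers plus replacements. It does not. Non-responders and patients who worsen are kept in follow-up, and other missing outcomes are imputed.
- A reader might illustrate the harm by swapping one or two iTBS non-responders for responders, so that 15/30 versus 8/30 (p = 0.063) becomes 16/30 (p = 0.035) or 17/30 (p = 0.018). That does not isolate the exclusion. With replacements enrolled and every randomised patient kept, the comparisons are 16/31 versus 8/30 (p = 0.046) and 17/32 versus 8/30 (p = 0.034), both already below 0.05. In those examples the crossing comes from the added responders.

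**Conclusion.** The contradiction is real and nothing else in the article resolves it. For patients who withdraw consent after randomisation, the plan promises intention to treat and also orders their exclusion and replacement. Followed as written, the second statement removes randomised patients from the primary analysis.

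The size is modest at the plan's own attrition figure: about 1 to 2 points of bias if 5% of one arm withdraws and all are non-responders, with almost no change in type I error. It becomes material only if withdrawals are more frequent and one-sided, or if the result is borderline. The p = 0.059 to 0.035 example shows that exclusion alone can then decide the chi-squared test.

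The withdrawal counts, their concentration in one arm, and the assumption that those who leave are non-responders are illustrative and do not come from the article.

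**What to change.** Replace the withdrawal sentence with a rule along these lines:

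- Exclusion and replacement apply only to patients who withdraw before randomisation.
- All randomised patients are analysed in their allocated arm, using data collected up to withdrawal unless the patient asks for erasure.
- A missing end-of-treatment MADRS is handled by the multiple imputation already planned, with a sensitivity analysis counting withdrawals as non-responders.
- Any extra recruits are additional and displace no randomised patient.

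This should be settled before the treatment allocation is known to those who analyse the data.

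The cost is a short text change and no required extra patients. Under multiple imputation the 60-patient basis need not change in principle, apart from a small loss of information. The sensitivity analysis has less power. With 5% withdrawal in each arm counted as non-response (assumption), the rates become 0.95 × 25% = 23.75% and 0.95 × 60% = 57%, and power at 30 per arm falls from 79.9% to 76.0%. With 10% (assumption) it is 72.0%.

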## Discussion

Depression is known as a difficult-to-treat disorder. By 2013, unipolar depression is expected to rank second out of the 15 most common disorders after AIDS and before ischemic heart disease [49]. The advantages of rTMS are numerous: it is painless, well-tolerated in terms of memory, cardiac, hepatic and renal functions as well as libido. There is no need for general anaesthesia with curarisation. Since the early 1990s, an increasing number of studies has focused on the therapeutic potential of rTMS in psychiatry [50].

This technique has a compliance rate of 97% (versus 60% traditionally recorded for medication). In fact, several meta-analyses based on randomised, controlled, double-blind studies refer to the therapeutic efficacy of rTMS in the management of resistant depression. The use of rTMS devices was also validated for this indication by the US Food and Drug Administration (FDA) in 2008 and by the European Union (EU) in 2012. By way of example, one of the most recent analyses highlighted a three-fold greater response and remission rate for left prefrontal cortex stimulation at high frequency versus placebo [10].

Furthermore, once antidepressants have failed, rTMS would be less expensive and would allow a better quality of life and greater function compared to conventional treatment strategies [51]. Its mechanisms of action are manifold: improvement in prefrontal hypometabolism [52] and neuromodulation of remote cerebral areas (especially the subgenual region) [53], regulation of the hypothalamo-hypophyseal axis [53], modulation of cortical excitability and synaptic plasticity [54–56] and dopaminergic secretion [57, 58].

The optimisation of alternative treatments for refractory or chronic depression is, therefore, a public health issue. The Theta Burst paradigm seems promising since 3 min of iTBS are essentially more effective and have a longer lasting effect than 20 min of conventional rTMS stimulation at 5 Hz (as evidenced in MEPs) [59]. In fact, iTBS tends to mimic the physiological rhythm of the human neocortex and involves the cerebral plasticity mechanisms responsible for positive and presumably longer-lasting effects [60], with a shorter, less intense stimulation mechanism [61]. Duprat et al., (2016) recently found a 30% remission rate (HDRS <7) after 2 weeks of accelerated (20 sessions/2 weeks) iTBS in a cross-over, sham-controlled design [48]. These facts suggest additional patient comfort, lower session costs and greater prevention of relapse. In the case of a prolonged effect, it could be an alternative to potentiating medicinal treatment (combinations of antidepressant, mood stabilising or adjuvant antipsychotic agents) with fewer compliance problems. The efficacy of Theta Burst was investigated in the management of resistant depression in two studies, which confirmed its superiority compared to placebo (Li et al., [18] with 30 subjects; Plewnia et al., [62] involving 60 subjects). Recently, in a larger sample but under natural conditions (retrospective study), iTBS was as clinically effective as HF-rTMS at 10 Hz but five times longer (6 versus 30 min, respectively) [19]. The authors concluded that these data should be confirmed by randomised controlled trials. Better targeting of the responder profile leads to better use of human and material resources in medical-economic terms. In cognitive terms, the planning assessed in the TMT, mental flexibility assessed using the MCST, or verbal fluency are influenced by rTMS treatment [63–67] and are, therefore, potential response markers. Psychomotor retardation has a predictive value in assessing the response for most biological treatments of depression [68]. Unlike cognitive functions, its pure motor component has not been assessed objectively to date in the context of the cerebral stimulation techniques used in the management of depression, for instance, with tasks such as the FTT or the prehensile motor strength test. The three main parameters affecting the motor cortex excitability are the CSP partly reflecting the activity of the gamma-aminobutyric acid (GABA)-B inhibitory circuits and double-pulse measurements including: SICI partly reflecting the activity of GABA-A IN inhibitors; and ICF partly reflecting the activity of glutamatergic IN activators. Two recent meta-analyses have highlighted changes in motor cortical excitability in an entire series of psychiatric disorders compared to healthy subjects [69, 70], with essentially an alteration in SICI and CSP during the depressive episode. In recent years, a few authors have focused on their potential as response markers, especially during noninvasive brain stimulation. In 2008, for instance, Lefaucheur et al., highlighted interhemispheric asymmetry of cortical excitability in depressed subjects: CSP and SICI were altered in the left hemisphere compared to the right and contrary to findings in healthy subjects [71]. Following cerebral stimulation (ECT and rTMS), Bajbouj et al. showed that CSP and SICI improved in responders and not in nonresponders [72].

To date and to our knowledge, this is the first trial aiming to investigate the comparative influence of iTBS and HF-rTMS on psychomotor retardation, executive functions and cortical motor excitability in depressed subjects. Psychomotor retardation could be corrected by the pro-dopaminergic effect of rTMS. Furthermore, executive functions may be a marker of the effect of DLPFC stimulation [73]. Given the data available on the effect of rTMS on magnetic resonance spectroscopy measurements, which indicate an increase in GABA and glutamate levels after rTMS [74, 75], neuromodulation can be assumed to manifest in the form of changes in cortical excitability measurements tending towards normalisation with 10-Hz protocols and iTBS, the greatest change being apparent in the case of the latter. The intensity of the gabaergic and/or glutamatergic deficit(s) and the degree of interhemispherical asymmetry in cortical excitability tests could identify responder patient profiles for both treatments. Moreover, measuring the difference in neurophysiological effect in both protocols would enhance the neurobiological understanding of this disease.

This sample is probably not entirely representative of a population often combining comorbidities with considerable treatment heterogeneity. However, we opted to limit the inclusion criteria in order to facilitate comparison with fewer confusing variables and interpret cortical excitability measurements.

